### Statistical issues and sample size

To determine the rather modest intervention effect of an absolute increase of 5% from an estimated baseline of 74% of VB, the following were noted:The rate of CSs in low-risk pregnant women is lower than in all pregnant women, since about one third of CSs are due to multiple births, breech presentations and prematurity or are elective.The primary endpoint in this trial is VB, which also includes OVBs.In sensitivity analyses, a risk ratio (RR) of 1.20 (95% confidence interval (CI) 1.05 to 1.38; two trials, 240 women) was documented for a spontaneous VB due to increased mobility and upright body positions in the first stage, but there was no statistically significant difference for OVB [6].An RR of 1.03 (95% CI 1.01 to 1.05) was found for the likelihood of spontaneous VBs in alternative birth settings, and an RR of 0.89 (95% CI 0.79 to 0.99) for the likelihood of OVBs (8 trials; *n* = 11,202) [14].

As the RR of 1.20 (see (c) above) for a spontaneous VB was calculated based on only two trials with a total of 240 women, we decided on a more conservative increase in the probability of VBs of 5%, i.e. from a baseline of 74% to 79%, corresponding to an RR of 1.07. This takes into account that the increase is more likely to be modest in those OUs where the rate of VBs is already higher. In addition, a smaller effect may be expected due to contamination bias if the same staff care for women in both trial groups.

Using a two-sided Fisher’s exact test, a sample of 3440 women would be required to detect a change of 5 absolute percentage points (from 74% to 79%) in the prevalence of VB (primary outcome) with a power of 90% (a significance level of 5%, assuming a dropout rate of 10%). The sample size has been enlarged to 3800 women to ensure there is sufficient power if there are deviations from the planning assumptions, e.g. increased dropout rates or different baseline rates in OUs recruited to replace study sites that prematurely withdraw from study participation.

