### Data analysis

Characteristics of the OUs (centres), study participants and outcomes are described separately for the intervention and control groups (depending on their distribution) using frequency tables, estimated probabilities, 95% CI, means ± standard deviations and percentiles. The analysis performed is intention to treat. In the primary analysis, the probabilities of a VB in the intervention and control groups are compared by Fisher’s exact test using a significance level of 5%. The risk difference and 95% CI are estimated. Additionally, randomised women with missing data in the primary outcome (e.g. dropouts) will be compared to the analysis set with respect to available characteristics, including statistical tests depending on their distribution (Fisher’s test, *t*-test or Wilcoxon rank sum test).

Sensitivity analyses for missing values will be performed in the full intention-to-treat population by multiple imputation, including adjustment for centre effects using logistic regression models with dependent variable VB (yes/no), random effects centre and intervention (versus control) as independent variable (reference for generalised linear mixed models [48]). A further logistic regression model will include an additional random effect of the interaction centre*intervention to adjust for possible centre effects on the intervention effect.

The following variables will be classified and included as independent variables in the logistic regression models above (with and without interaction with intervention) to investigate the role of potential clinically relevant prognostic factors which include: annual baseline rates of VBs of participating OU, age, body mass index, parity, induction of labour with allopathic medicine on admission to birthing room and fear of childbirth.

Five binary, log-normally and ordinally distributed *secondary outcomes* will be compared between the intervention and control groups by Fisher’s test, *t*-test (after a log-transformation if necessary) and Wilcoxon’s test. Multiple testing (five tests) will be adjusted by the Bonferroni method using a reduced significance level of 1%. No imputation is planned for the secondary outcomes.

All tests are two-sided unless otherwise stated. No interim analyses are planned, with the exception of a descriptive analysis to ensure safety (Section 2.11).

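### The interaction of intervention with the OU's baseline VB rate, which rests on 12 units, is also to be fitted in the model with only a random centre intercept; if effects vary between OUs, that model overstates its precision

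*Protocol article*

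**What the plan says.** All the modelling text is in the Data analysis section of the Protocol article. The logistic models appear as sensitivity analyses around the primary Fisher test. The first has "random effects centre and intervention (versus control) as independent variable", that is, a random centre intercept and a fixed intervention effect. A further model adds a random effect for centre by intervention, with the stated aim of allowing for centre effects on the intervention effect.

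The next paragraph says: "The following variables will be classified and included as independent variables in the logistic regression models above (with and without interaction with intervention"). The list opens with "annual baseline rates of VBs of participating OU" and continues with age, body mass index, parity, induction of labour and fear of childbirth. Models is plural and no variable is singled out, so on the natural reading the interaction of intervention with the OU rate is fitted in both models. The section does not say which model decides for this variable.

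The Design section gives 12 OUs. The sample size section remarks that "the increase is more likely to be modest in those OUs where the rate of VBs is already higher".

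**The concern.** Five of the six listed variables differ from woman to woman. The OU's baseline VB rate takes one value per OU, so the evidence on whether it modifies the effect consists of 12 OU-specific intervention effects.

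A random centre intercept absorbs differences in the level of VB between OUs. It does not absorb differences in the intervention effect. Without a random centre-by-intervention term, any leftover variation of the effect between OUs is treated as if it were only sampling error among women. Some of it can then be credited to the OU rate with unjustified precision.

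The protocol names possible sources of such variation:
- Control rooms differ, some already holding a birthing stool, suspended fabric or an exercise ball (Control).
- The delivery bed may be absent or only hidden (Intervention).
- Shared staff may cause contamination, and replacement sites may have different baseline rates (Statistical issues and sample size).

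At stake is a claim about whether the redesigned room works differently in OUs with high and low VB rates. Two results would be available for it, one of them possibly too precise, with no rule of precedence.

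**Working it through.** **Inputs from the Protocol article.** VB 74% v 79%, two-sided 5%, power 90%, dropout 10%, N = 3,440 enlarged to 3,800 (Statistical issues and sample size); 12 OUs (Design); 1:1 allocation stratified by OU and parity (Randomisation).

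**Assumed.** The between-OU SD of the log odds ratio, τ, for which the protocol gives no value; range 0 to 0.3. OUs of equal size unless stated.

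**1. The plan's own figure.** The plan states that "a sample of 3440 women would be required". The two-proportion formula with continuity correction gives 1,549 per arm, 3,098 in total, and 3,098 / 0.90 = 3,443. This reproduces 3,440. The plan gives no figure for the interaction.

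**2. Sampling variance within one OU.** With 3,800 / 24 = 158.3 women per arm per OU, the variance of an OU's log odds ratio is

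v = 1/(158.3 × 0.74 × 0.26) + 1/(158.3 × 0.79 × 0.21) = 0.0328 + 0.0381 = 0.0709.

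**3. Understatement of the standard error.** For six OUs against six, the random-intercept model takes the variance of the contrast as v(1/6 + 1/6). The true value is (v + τ²)(1/6 + 1/6). The ratio of true to model SE is therefore √(1 + τ²/v), and the type I error is 2[1 − Φ(1.96 / ratio)]. At τ = 0.2: √(1 + 0.04/0.0709) = 1.25, 1.96/1.25 = 1.57, giving 11.7%.

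**4. Simulation, no true modification by the OU rate.** A random-intercept logistic mixed model was fitted by maximum likelihood with the OU rate split at the median (600 trials per setting, Monte Carlo SE 0.9 to 1.6 points). A faster two-stage version (3,000 trials per setting) covered equal and unequal OU sizes and a two-class or continuous OU rate. Both drew OU baseline logits with SD 0.25 around 74%.

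| τ | True SE / model SE | Type I error, formula | Mixed model | Two-stage, range |
|---|---|---|---|---|
| 0 | 1.00 | 5.0% | 4.7% | 4.5–5.0% |
| 0.1 | 1.07 | 6.7% | 7.2% | 5.4–7.3% |
| 0.2 | 1.25 | 11.7% | 12.3% | 10.4–13.0% |
| 0.3 | 1.51 | 19.3% | 19.0% | 17.3–20.8% |

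With 10% dropout (N = 3,420, v = 0.0788) the formula gives 5.0%, 6.5%, 11.1% and 18.1%.

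**5. Scale of τ.** At a control rate of 74% and an average gain of 5 points, 95% of OU-specific risk differences lie between +1.6 and +8.1 points at τ = 0.1, between −2.2 and +10.8 at 0.2, and between −6.4 and +13.1 at 0.3.

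**6. With the between-OU variance in the model (two-stage simulation, τ from 0 to 0.3).** A plain Wald z test rejects in 3.3–4.8% at τ of 0 to 0.1 and in 6.0–7.9% at 0.2 to 0.3. A t reference on 12 − 2 = 10 df with the Knapp-Hartung variance rejects in 4.2–5.6% throughout. A t(10) reference without that variance is conservative at small τ (1.3–2.9% at 0 to 0.1).

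**The case against.** **The valid model is already planned, and precedence between models is a matter for the SAP.** The first half is true and limits the point. The second half does not remove it: the article assigns the interaction to both models, so this is a stated analysis, not detail left out.

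**The harm is conditional.** This stands. A reader might infer that the random-intercept p-value and interval are simply wrong. The document does not support that, because there is no inflation at τ = 0 and little at 0.1, and no τ is given.

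**The remark on high-rate OUs does not predict an interaction.** A reader might take "the increase is more likely to be modest in those OUs where the rate of VBs is already higher" as showing that the log odds ratio varies, or that this interaction will be reported as showing which hospitals benefit. Neither follows. The remark justifies a cautious effect size and concerns absolute gains, which a constant odds ratio partly produces. With the planned odds ratio of (0.79/0.21)/(0.74/0.26) = 1.32, 74% rises by 5.0 points, whereas 80% rises by only 4.1 (odds 4 × 1.32 = 5.29, or 84.1%). The stated purpose is to look at prognostic factors, and the planned subgroup analysis concerns parity.

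**The bracket might refer to the models with and without the centre-by-intervention term.** Then no fixed interaction with the OU rate would be planned. This cannot be ruled out, but the bracket speaks of interaction with intervention, does not mention centre, and qualifies how the listed variables enter. The reading used here is the more natural one.

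**Conclusion.** The point holds in a limited form. For the OU's baseline VB rate alone, the random-intercept model is not a sound basis for inference on effect modification, because the variable has 12 independent units and the model does not allow the effect to vary between them. If such variation exists, intervals should be about 7%, 25% and 51% wider at τ = 0.1, 0.2 and 0.3, with false-positive rates of about 7%, 12% and 19% instead of 5%. These sizes rest on the assumed τ, on 12 OUs and on about 3,800 women.

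The point concerns one exploratory coefficient in one of two planned models. The Fisher test, the risk difference, the sample size, the secondary outcomes and the parity subgroups are untouched.

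**What to change.** Add one sentence: inference on intervention by OU baseline VB rate rests only on the already planned model with the random centre-by-intervention effect, with a small-sample t or F reference (about 10 df for a two-class or linear term; fewer with more classes). A plain Wald z test would leave some excess at larger τ. The random-intercept model can stay for the woman-level variables. Whether the OU rate is classified, as planned, or kept continuous is optional; the two behaved alike in the simulation.

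The cost is a wider interval for this one interaction. No change to data collection, the primary analysis or the sample size is needed.

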#### Subgroup analysis

Subgroup analyses are planned for two parity strata (primiparae and multiparae) and the primary outcome (VB). Subgroup analyses will be performed with respect to the primary outcome using logistic regression analyses. The primary outcome is the dependent variable. Centres are random effects. Independent variables are intervention versus control, subgroup indicators, and the interaction between subgroup and intervention/control.

An additional model including previous CSs as a further independent variable will be fitted in the subpopulation of multiparae only.

The whole analysis will be repeated as a per protocol analysis on the subpopulation after exclusion of participants with protocol violations (expected to be about 10%) or missing values in the primary outcome.

#### Health economics evaluation

As part of the trial, a cost-effectiveness analysis and a cost–benefit analysis will be performed from two perspectives: that of the statutory health insurance and that of the clients (mother and infant) [49]. The analysis to estimate the cost-effectiveness of the intervention in terms of additional costs per additional VB will be performed by calculating an incremental cost-effectiveness ratio, i.e. the ratio of the difference in costs between the intervention group and the control group divided by the difference in the number of VBs. The effect parameter is the primary outcome and will be taken from the trial. The cost–benefit analysis will relate associated costs to participants’ willingness to pay for the use of a redesigned birthing room (such as the intervention room).

Cost parameters will be collected on the postnatal ward before discharge from hospital (*t*_2_) and at 3 months postpartum (*t*_3_). Heath utilisation costs for both mother and baby will be considered, in particular, those related to birth, postpartum health care, hospitalisations (child) and doctor visits (mother and child). Moreover, medication, household help, breastfeeding aids and baby food will be assessed by a questionnaire. Resource use associated with the intervention, i.e. equipment in the birthing room, will be derived from the study documentation. Costs explicitly associated with study conduct, such as data collection or process evaluation, will not be taken into account.

Statistical analyses will be based on intention to treat. Mean differences between intervention and control groups for costs and effects will be calculated. The 95% CIs will be obtained parametrically for the incremental cost-effectiveness ratio according to Fieller’s theorem and non-parametrically by a bootstrap procedure [50]. Univariate and probabilistic sensitivity analyses will be performed to estimate the robustness of the incremental cost-effectiveness ratio. Additionally, a budget impact analysis will estimate the financial consequences for the statutory health insurance in case the programme proves to be cost-effective [51, 52].

All statistical analyses will be done by an independent statistician.

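### The stated cost-effectiveness intervals are for the ICER alone and become uninformative when the vaginal birth difference is not significant; maternal readmission is not named as a cost

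*Protocol article*

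**What the plan says.** All of the following stands in the Health economics evaluation section of the protocol article.

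- **Measure.** The cost-effectiveness result is an ICER, defined as "the ratio of the difference in costs between the intervention group and the control group divided by the difference in the number of VBs".
- **Components.** "Mean differences between intervention and control groups for costs and effects will be calculated".
- **Intervals.** "The 95% CIs will be obtained parametrically for the incremental cost-effectiveness ratio according to Fieller’s theorem and non-parametrically by a bootstrap procedure".
- **Sensitivity.** "Univariate and probabilistic sensitivity analyses will be performed to estimate the robustness of the incremental cost-effectiveness ratio".
- **Decision.** A budget impact analysis follows "in case the programme proves to be cost-effective". No criterion for that judgement is given.
- **Cost scope.** The sentence on costs opens "Heath utilisation costs for both mother and baby will be considered, in particular" and its list includes "hospitalisations (child) and doctor visits (mother and child".

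A separate cost–benefit analysis relates costs to what participants would pay for use of a redesigned room.

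**The concern.** The ICER has the VB difference in its denominator. If the data cannot exclude a zero difference, a confidence set for the ratio cannot be a finite interval. A bootstrap percentile interval always returns two finite numbers, but that does not solve the problem. Once replicates fall on both sides of a zero effect, a negative ratio can mean cheaper with more VBs (dominant) or dearer with fewer VBs (dominated), so ranking the ratios has no consistent meaning.

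At stake is the step from the interval to the cost-effectiveness judgement that triggers the budget impact analysis. The planned sensitivity analyses address the same ratio and inherit the difficulty.

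The second matter is scope. The Background section links caesarean section (CS) to greater maternal morbidity, and one of the two perspectives is that of the statutory health insurance. Maternal readmission is therefore a cost that might differ between arms, yet hospitalisations carry a child-only tag beside doctor visits that name both mother and child.

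**Working it through.** **1. Inputs** (Statistical issues and sample size; Recruitment and randomisation). VB rates 74% and 79%, two-sided 5% level, 90% power, 10% dropout, 3,440 women enlarged to 3,800, allocation 1:1.

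**2. The plan's own sample size.** The usual two-proportion formula is n = [1.96·√(2·0.765·0.235) + 1.2816·√(0.74·0.26 + 0.79·0.21)]² / 0.05², which gives 1,510 per arm. With the continuity correction, as an approximation to Fisher's exact test, it gives 1,549 per arm. Then 2 × 1,549 / 0.90 = 3,443, against 3,440 stated. The plan's figure reproduces, so the same rates and sizes can be used for the precision of the ICER denominator.

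**3. When the Fieller set is bounded.** Let dC and dE be the cost and effect differences, with standard errors sC and sE and covariance sCE. The set contains every R with (dC − R·dE)² ≤ 1.96²·(sC² − 2R·sCE + R²·sE²). The coefficient of R² is dE² − 1.96²·sE². The set is a finite interval only if this is positive, that is, if |dE|/sE > 1.96. Otherwise it is two disjoint rays or the whole line.

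**4. How often that fails.** For true difference d and m women per arm, sE = √[(0.74·0.26 + (0.74+d)(0.26−d))/m] and P(unbounded) = 1 − [Φ(d/sE − 1.96) + Φ(−d/sE − 1.96)]. Example: d = 0.05, m = 1,710 gives sE = 0.0145, d/sE = 3.45 and P = 6.8%.

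| True VB difference | 3,096 analysed (3,440 × 0.9) | 3,420 analysed (3,800 × 0.9) | 3,800 analysed |
|---|---|---|---|
| 5 points | 9.2% | 6.8% | 4.6% |
| 4 points | 25.8% | 21.7% | 17.6% |
| 3 points | 50.7% | 46.8% | 42.4% |
| 2 points | 74.9% | 72.8% | 70.4% |
| 1 point | 90.2% | 89.7% | 89.1% |
| none | 95.0% | 95.0% | 95.0% |

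The observed difference must exceed about 2.7 to 3.1 points (1.96·sE) for a finite interval.

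**5. Is a smaller effect realistic?** The sample size section cites a risk ratio of 1.03 for spontaneous VB in alternative birth settings. Applied to all VBs (an assumption), it gives 0.74 × 1.03 = 76.2%, and the Fieller set would be unbounded in 65% to 70% of trials across the three sizes. The same source gives 0.89 for operative VB, which would make the combined gain smaller.

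**6. What the set looks like.** The document gives no costs, so take purely illustrative figures: dC = 50 currency units, sC = 40, sE = 0.0146, no correlation.

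- dE = 0.05: −606 to 3,580 per additional VB.
- dE = 0.03: −1,178 to 38,158.
- dE = 0.025: every value except those between −11,218 and −1,677.
- dE = 0.02: the whole line.

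**7. Bootstrap.** By the same normal approximation, with 3,420 analysed and an observed difference of 2 points, Φ(−0.02/0.0148) ≈ 9% of replicates have a negative effect difference. At 1 point it is 25%; at 5 points it is 0.03%. Whenever |dE|/sE < 1.96, more than 2.5% of replicates lie on the other side of zero, enough to disturb a 95% percentile interval.

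**8. The alternative.** Incremental net benefit at willingness to pay λ per additional VB is λ·dE − dC, with variance λ²·sE² + sC² − 2λ·sCE. It has no denominator, so its interval is always finite. Its value cannot be computed here, because no cost, standard deviation or λ is given.

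**9. Cost list.** The lead-in covers mother and baby. The items are birth, postpartum health care, hospitalisations tagged for the child, and doctor visits tagged for both. The Data collection and outcome measures section records length of stay on the postnatal ward and, at 3 months, maternal and infant health and utilisation costs. Nowhere is maternal readmission named as a cost item.

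**The case against.** Fieller and bootstrap intervals are recognised methods, and the plan uses both. An unbounded Fieller set is a truthful report that the data do not exclude a zero denominator. That stands: the method is valid but uninformative in this case.

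A reader might infer that the whole economic result would then be uninterpretable. The document does not support this. Cost and effect differences are planned separately, the risk difference has its own 95% CI in the Data analysis section, and a cost–benefit analysis is also planned. That last analysis values use of the room, however, and not an additional VB, so it does not replace an interval for cost per additional VB. At the planned effect the difficulty is uncommon. It also depends on a difference not significantly different from zero, rather than on one that is not positive: a clearly negative effect gives a bounded interval, of ambiguous sign.

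A reader might also take "divided by the difference in the number of VBs" to mean raw counts that shift with arm size. The later statement on mean differences, and a primary outcome compared as probabilities, resolve this in favour of a per-woman ratio.

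Finally, a reader might conclude that maternal hospital costs are left out. The lead-in covers both mother and baby and marks the list as illustrative, and birth and postpartum care can carry the mother's initial stay. What remains is that later maternal readmission is unnamed beside a child-only tag.

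A fuller health-economic plan, not shown, may contain net benefit or an acceptability curve. Their absence from an article is not the point. The point is that the one interval method stated fails to inform whenever the VB difference is not significant.

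**Conclusion.** The point holds in limited form. The only stated cost-effectiveness intervals are for a ratio. They lose their use in about 5–7% of trials at the planned 5 points (9% if only 3,096 women are analysed), about 70–73% at 2 points and 95% with no effect. In those cases they cannot settle whether the programme is cost-effective. The primary analysis is unaffected.

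The figures assume a 74% control rate, equal arms, a normal approximation with unpooled standard errors, and no allowance for centre or parity. The correspondence with a non-significant Fisher test is therefore close but not exact.

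On costs, the document supports a request to clarify whether maternal readmission is counted. If CS raises readmission and this is not costed, savings would be understated, but no readmission rate or unit cost is given and the size of any bias cannot be computed.

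**What to change.** 1. From the same bootstrap replicates, report incremental net benefit with a 95% CI over a stated range of willingness to pay per additional VB, a cost-effectiveness acceptability curve and the cost-effectiveness plane.
2. Give the ICER as a point estimate, defined as the mean cost difference per woman divided by the difference in VB proportion.
3. State in net-benefit terms what would count as cost-effective for the purpose of starting the budget impact analysis.
4. Reconcile the child-only tag on hospitalisations with the stated scope of mother and baby by costing maternal readmissions up to 3 months.

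The cost is some wording in the analysis plan, a little more output and at most one item on the 3-month questionnaire, if it does not already ask.
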